3.2.7 Refusal to sign the informed consent

3.2.8 Refusal to participate in the Swallow Preservation Program prior to start of Soylent if applicable.

3.2.9 Evidence of clinically significant swallowing dysfunction by history or physical exam at time of radiation oncology consultation

3.2.10 Distant metastatic disease (M1 disease)

## **4.0 REGISTRATION PROCEDURES**

### **4.1 General guidelines**

Patients seen at UCLA in the Department of Radiation Oncology and recommended for definitive or adjuvant chemoradiation for locally advanced head and neck cancer will be informed of this clinical trial if eligible. The decision to participate will be voluntary. Eligible patients who decides not to participate will continue to be offered standard chemoradiation therapy with standard supportive care (including nutritional counseling, oral nutritional supplementation with commercially available supplements, and/or therapeutic G-tube placement at 10% weight loss).

### **4.2 Registration Process**

Informed consent form will be given to the patient for review. Consent will be obtained after a clear and thorough discussion between the patient and the study investigator in clinic. When practical and in the best interest of the subject, the consent discussion may occur by telephone/telemedicine. The IRB-approved informed consent document may be sent to the subject electronically to be signed and returned electronically to the investigator for counter-signature. To register a patient, the research coordinator will obtain or complete: (1) documentation of locally advanced head and neck cancer for which chemoradiation has been recommended (2) successful taste test of Soylent™ nutritional supplement (3) signed informed consent form; (4) signed HIPAA authorization form.

Prior to confirmation of eligibility and enrollment in the study, the following will be obtained anytime in advance of beginning chemoradiation: (1) Total amount of blood samples that can potentially be collected 82.5 mL (27.5 mL at each draw), (2) cheek swabs sample, (3) quality of life assessments.

## **5.0 TREATMENT PLAN**

### **5.1 Radiation Simulation and Planning**

Enrolled patients, after confirmation of eligibility, will undergo standard radiation simulation and treatment planning for their head and neck cancer. Intensity-modulated radiation therapy (IMRT) techniques will be required for enrollment on this study.

The responsible study investigator(s), will delineate the regions of gross tumor volume (GTV) using all available imaging. Clinical target volume(s) (CTVs) will be delineated to account for regions at risk for harboring subclinical disease. Planning target volume(s) (PTVs) will be delineated by expansions to the CTV(s) to account for patient set-up error and motion.

Delineation of normal critical structures of the head and neck will be performed, including the brain, brainstem, spinal cord, eyes, lens, optic chiasm, optic nerves, oral cavity, lips, mandible, salivary glands, pharynx, esophagus, larynx, and cochlea. The radiation physicist will optimize the radiation therapy treatment plan and the responsible study investigator(s) will review it prior to approval for treatment. Dose volume histograms (DVH), and normal tissue constraint parameters specified below will be used to judge the quality of the plan and optimize doses to the PTV(s) as well as maximally sparing of organs at risk (OARs).

Treatment will be delivered in 30-35 daily sessions (Monday-Friday) lasting 15-30 minutes in the Department of Radiation Oncology.

## **5.2 Chemotherapy**

Enrolled patients, after confirmation of eligibility, will undergo concurrent chemotherapy according to the prescription of their medical oncologist. Chemotherapy regimens may include weekly cisplatin (50 mg/m^2), bolus q3week cisplatin (100 mg/m^2), or weekly cetuximab (400 mg/m^2 loading dose with 250 mg/m^2 weekly infusion), although other chemotherapy regimens are permitted by medical oncologist preference. Infusions will occur in the hematology/oncology infusion center, and serum chemistries and complete blood count will be taken and reviewed per standard protocol during chemotherapy.

## **5.3 Baseline Nutritional, Metabolic, & QOL Assessments**

Prior to beginning chemoradiation, baseline serum samples, cheek swab samples, body weight, and body mass index will be obtained. This may be collected at the time of consent. A panel of germ-line biomarkers predicting radiation-related toxicity will be incorporated to control for baseline differences in radiosensitivity. Baseline labs will be drawn along with necessary pre-treatment labs for chemoradiation to minimize patient inconvenience and discomfort. All patients will be asked to fill out patient-reported quality of life (QOL) questionnaires (UW-QOL and FACT-HN). All patients will have a clinical nutritional assessment by the study dietitian prior to initiating treatment or within the first week ( $\leq 5$  treatment sessions) of treatment.

All patients will participate in the Swallow Preservation Program in the Speech Pathology Clinic. They will begin participation within one week ( $\geq 5$  treatment sessions) of initiating chemoradiation. They must pass the Clinical Swallow Evaluation (CSE) that occurs during the Swallow Preservation Program initial assessment or deemed to have a functional oropharyngeal swallow with a Modified Barium Swallow Study (MBSS) if unable to pass the CSE for continuation in the study. Teaching to minimize dysphagia will be administered, and evaluation for evidence of aspiration will also be done throughout participation in the Swallow Preservation Program.

## **5.4 Weekly On-Treatment Management & Nutritional Supplementation**

Weekly during treatment, patients will have their body weight, body mass index, and nutritional status (oral intake) assessed by the dietitian. If the dietitian is unavailable, a member of the clinical team will evaluate body weight and body mass changes, as well as take estimates of oral intake. The body weight at the first on-treatment visit during chemoradiation will be compared to the body weight taken at the time of enrollment. If a patient has gained weight, this new body weight will be used as the baseline weight from which weight loss will be determined. However, if weight loss occurs from enrollment, the baseline body weight will remain the body weight at the time of enrollment. Patients will also have weekly assessment of physician-reported acute toxicities during weekly on-treatment visits with the treating radiation oncologist.

The radiation oncologist, in conjunction with the dietitian, will determine whether the patient has lost 5% of body weight from baseline, indicating the need to initiate oral nutritional replacement with Soylent™. The dietitian will record weekly oral intakes for all patients, including the use of oral nutritional replacement. Patients will be monitored through the Swallow Preservation Program for evidence of aspiration.

Once 5% body weight loss is seen, patients will be given a small supply of Soylent™ from the clinic while awaiting their home order to be filled. In order to receive this delivery, patients will be

given a voucher for online redemption, with which they will sign up for delivery from Soylent™. Soylent™ will not ask for any information in addition to what is standardly required for delivery service. Please see Appendix for a screenshot of this sign-up process.

Compliance with oral nutrition replacement is defined as continuing at least 50% of recommended supplementation with Soylent™ as recommended by dietitian. If a patient stops all use of Soylent™ during treatment without resumption (and dietitian recommendation is for continued use of oral nutritional supplementation), this will be considered non-compliance. If a patient is maintaining weight on regular nutrition without supplementation, or proceeds with G-tube placement, stopping Soylent™ supplementation will not be considered non-compliance. If a patient is found to have evidence of aspiration in the Swallow Preservation Program, discontinuation of Soylent™ replacement will not be considered non-compliance. If a patient refuses to resume Soylent™ (and is considered non-compliant), alternative nutritional recommendations will be given to the patient from the dietitian and treating radiation oncology team. Using other nutritional supplementation in addition to Soylent™ (including regular food, other commercially available shakes, etc.) will not be considered non-compliance. However, it will be noted in the nutritional record that the patient is using means in addition to Soylent™ for nutrition.

Early G-tube insertion if it is in the best medical judgement by the treating physicians may be done prior to the 10% weight loss. If a patient loses >10% of weight and is determined to necessitate a G-tube due to poor oral nutritional intake by the treating radiation oncologist, in conjunction with the dietitian assessment, a therapeutic G-tube will be recommended for the patient. Therapeutic G-tube placement will be performed by the interventional radiology or gastroenterology services at the study site. Upon completion of concurrent chemoradiation (last day of treatment), a second set of serum/cheek swab samples will be collected along with repeat UW-QOL and FACT-HN questionnaires. These labs will again be drawn along with necessary on-treatment labs for chemoradiation to minimize patient inconvenience and discomfort.

### **5.5 Patient Follow-Up after Treatment**

Patients will be followed clinically after treatment per standard of care, including routine evaluation of patient-reported QOL metrics (UW-QOL and FACT-HN questionnaires), physician-reported acute and late toxicities, body weight, and clinical/radiographic evaluations for local/locoregional recurrence, and distant metastases. A patient death, and its cause, will be recorded by the treating radiation oncologist in the study records if this occurs. Patients will continue routine follow-up visits in radiation oncology at approximately 1, 3, 6, 12, 16, 18, and 24 months as is routine at our institution for patients with locally advanced head and neck cancer surveillance. When practical and in the best interest of the subject, follow-up visits may occur via telemedicine. The UW-QOL and FACT-HN questionnaires may be administered electronically or by telephone. Serum (50 mls)/cheek swab samples will be taken only at the conclusion of chemoradiation (in the last week of treatment, as noted above) and at the 3-month follow-up visit. The 3-month follow-up visit labs will attempt to be drawn with necessary labs, if needed. Otherwise, this will be a separate blood draw. All serum and cheek swab sampling done for basic science research (i.e., those described in this section) will occur only when feasible

## **6.0 PHARMACEUTICAL INFORMATION**

### **6.1 Investigational Agent or Device**

Not applicable

**6.2 Availability**

Not applicable

**6.3 Agent Ordering**

Not applicable

**6.4 Agent Accountability**

Not applicable

**7.0 ADVERSE EVENTS: LIST AND REPORTING REQUIREMENTS**

Toxicity assessment will be performed using the National Cancer Institute Common Terminology Criteria for Adverse Events (CTCAE) version 4.0 for early ( $\leq 3$  months), and late ( $> 3$  months) radiation toxicity. This study's intervention is the addition of Soylent™ oral nutritional replacement triggered by 5% weight loss from baseline to standard chemoradiation for locally advanced head and neck cancer. The interaction of this nutritional supplement with radiation and chemotherapy toxicities is unknown but no specific toxicities are predicted as compared to patients undergoing standard chemoradiation treatment with standard supportive care measures.

**7.1 Soylent™ Oral Nutrition Supplement-Related Toxicities**

As Soylent™ is a commercially-available nutritional supplement/meal replacement agent with no known side effects, we do not specifically anticipate side effects from its use. Since it needs to be swallowed, potential adverse events in the mouth or throat are possibilities, including worsened oral mucositis, dysgeusia, dysphagia, or xerostomia which are known radiation and/or chemotherapy-related toxicities for chemoradiation to the head and neck. Since Soylent™ may also impact the gastrointestinal system as a food, increased esophagitis, nausea/vomiting, dyspepsia, constipation, diarrhea, flatulence, and abdominal pain are possibilities. A food allergic reaction, including anaphylaxis, is a possibility. Possible additional toxicities may include exacerbation of any other radiation-related or chemotherapy-related toxicity due to an unknown mechanism.

## 8.0 STUDY CALENDAR

| Study procedures                                                      | Screening      | Pre-CRT         | CRT            | Post treatment visit
(months following chemoradiation) |                |   |    |    |    |    |    |
|-----------------------------------------------------------------------|----------------|-----------------|----------------|-----------------------------------------------------------|----------------|---|----|----|----|----|----|
|                                                                       |                |                 |                | 1                                                         | 3              | 6 | 12 | 16 | 18 | 24 | ET |
| IMRT                                                                  |                |                 | X              |                                                           |                |   |    |    |    |    |    |
| Chemotherapy                                                          |                |                 | X              |                                                           |                |   |    |    |    |    |    |
| Informed Consent                                                      | X              |                 |                |                                                           |                |   |    |    |    |    |    |
| Demographics                                                          | X              |                 |                |                                                           |                |   |    |    |    |    |    |
| Medical History                                                       | X              |                 |                |                                                           |                |   |    |    |    |    |    |
| Initial Consultation with Radiation Oncology                          | X              |                 |                |                                                           |                |   |    |    |    |    |    |
| Initial Consultation with Medical Oncology                            |                | X               |                |                                                           |                |   |    |    |    |    |    |
| Initial Consultation with the dietitian                               |                | ***X            |                |                                                           |                |   |    |    |    |    |    |
| Urine Pregnancy Testing/Pregnancy Waiver as Clinically Indicated*     | X              |                 |                |                                                           |                |   |    |    |    |    |    |
| Radiation Treatment Planning: CT, PET-CT, and/or MRI-based simulation |                | X               |                |                                                           |                |   |    |    |    |    |    |
| Swallow Preservation Program                                          |                | ***X            | X**            | X**                                                       |                |   |    |    |    |    |    |
| Weekly On-Treatment Visit with Radiation Oncologist                   |                |                 | X              |                                                           |                |   |    |    |    |    |    |
| Weekly On-Treatment Visit with the dietitian                          |                |                 | X              |                                                           |                |   |    |    |    |    |    |
| Body Weight Measurement/BMI Calculation                               | X              | X               | X              | X                                                         | X              | X | X  | X  | X  | X  | X  |
| Research Blood and Cheek Swab Sampling                                | X a | ⊗X a | X a |                                                           | X a |   |    |    |    |    |    |
| Soylent™ Oral Nutrition Replacement                                   |                |                 | X              |                                                           |                |   |    |    |    |    |    |
| Follow-up visit                                                       |                |                 |                | X                                                         | X              | X | X  | X  | X  | X  | X  |
| QOL Questionnaires (UW-QOL and FACT-HN)                               |                | X               |                | X                                                         | X              | X |    | X  | X  |    | X  |

\*Pregnancy testing/pregnancy waiver is given in our department as clinically indicated prior to the administration of radiation therapy (pre- or peri-menopausal woman under the age of 55 years)

\*\*Patients will attend swallow preservation program sessions as determined by the Speech Pathology Clinic team. This

may include sessions during or following chemoradiation.

CRT= chemoradiation

\*\*\* Must occur within one week ( $\geq 5$ ) treatment sessions of initiated chemo-radiation.

Routine follow-up visits every 3 months for the first year and every 4 months in the second year.

⊗ Pre-treatment (Baseline) labs, if not already collected at consent.

a Collect the final translational lab draw/ Swab collection at the last week of end of RT treatment. All saliva and blood collection done for basic science research purposes will occur whenever feasible.

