**DURATION OF INTERVENTION AND EVALUATION:**

Nutritional supplementation will take place if weight loss exceeds 5% from the baseline weight taken at study enrollment during concurrent chemoradiation. This is expected to occur in approximately 90% of patients undergoing chemoradiation from our institutional historical control data. Nutritional supplementation may continue until the month following completion of chemoradiation (up to approximately 3 month's total). Patients will be evaluated weekly by the study site's clinical dietitian and clinical staff to assess weight changes as is done for all patients undergoing chemoradiation to the head and neck. Patients will remove their shoes, items from their pockets, and any coats or sweaters. The dietitian and study staff will also determine the amount of supplementation utilized and assess the need of a G-tube during chemoradiation. G-tube placement will be recommended if a patient reaches 10% weight loss and/or is not meeting nutritional requirements as assessed by a dietitian. Patients will be required to be in a swallow preservation program with the Speech Pathology Clinic for minimizing dysphagia and aspiration surveillance. Clinical nutritional follow-up will continue as long as the patient is recommended to have nutritional supplementation. Weight measurements will be routinely taken at every follow-up visit. Blood/cheek swab sample collection (whenever feasible) for future analysis may occur at baseline (prior to treatment), at the conclusion of treatment (last week of chemoradiation), and at the 3-month follow-up visit. The University of Washington Quality of Life (UW-QOL) and Functional Assessment of Cancer Therapy Head & Neck (FACT-HN) questionnaires will be used

to assess QOL prior to beginning chemoradiation and at every routine follow-up after completing chemoradiation. Routine clinical follow-up will last for a minimum of 2 years.

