### **10.2.2. Analysis of Secondary Endpoints**

Weight loss and body mass index (BMI) will be collected at each visit and summary descriptive statistics will be calculated at each time points. Repeated measure ANOVA will be used to explore if there are any change in these parameters over time. Treatment breaks will be recorded in days per study patient and summarized. G-tube placement timing will be recorded for patients receiving G-tubes, and the duration of G-tube dependence will be recorded in days per study patient and summarized.

Serum HPV DNA, pre-albumin, albumin, C-reactive protein (CRP), interleukin-6 (IL-6), tumor necrosis factor (TNF), Vitamin A, Vitamin C, Vitamin D, tryptophan, kynurenine, leptin, and adiponectin, complete metabolic panel, and complete blood count and radiosensitivity biomarker panel will be summarized by descriptive statistics by visit time points, and these statistics will be plotted graphically.

Patient-reported QOL according to the University of Washington (UW-QOL) and Functional Assessment of Cancer Therapy-Head & Neck (FACT-HN) questionnaires will be summarized by descriptive statistics by visit time points.

The Kaplan-Meier method will be used to estimate time-to-event endpoints such as local/locoregional control, distant metastasis-free survival and overall survival. Summaries of the number and percentage of patients who have metastasized cancer/died, are still in survival follow-up, are lost to follow-up and have withdrawn consent will be provided along with median distant metastasis-free survival/overall survival.

As exploratory analyses, we will compare these secondary outcome measurements from our study with the control group or previously conducted studies available in the literature to evaluate the potential benefits of adding Soylent™ oral nutrition meal replacement in patients with head & neck cancer undergoing definitive or adjuvant chemoradiotherapy.

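### The study calendar leaves out quality-of-life questionnaires at the end of chemoradiation and at 12 and 24 months, which the protocol text requires: 3 of 9 scheduled assessments

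*Protocol*

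**What the plan says.** Four places in the Protocol text set the timing of the UW-QOL and FACT-HN questionnaires.

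- **Synopsis, Duration of Intervention and Evaluation:** the questionnaires are used "to assess QOL prior to beginning chemoradiation and at every routine follow-up after completing chemoradiation".
- **Section 5.3 (baseline):** "All patients will be asked to fill out patient-reported quality of life (QOL) questionnaires (UW-QOL and FACT-HN)".
- **Section 5.4 (last day of treatment):** "a second set of serum/cheek swab samples will be collected along with repeat UW-QOL and FACT-HN questionnaires".
- **Section 5.5 (follow-up):** follow-up is described as "including routine evaluation of patient-reported QOL metrics (UW-QOL and FACT-HN questionnaires)", with visits at "approximately 1, 3, 6, 12, 16, 18, and 24 months".

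The calendar in section 8.0 has its own row, "QOL Questionnaires (UW-QOL and FACT-HN)". It is marked at Pre-CRT, 1, 3, 6, 16 and 18 months, and ET (not spelled out there; read here as early termination). It is empty under Screening, CRT, 12 months and 24 months. In the same table, the follow-up visit and body weight rows are marked at both 12 and 24 months.

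For the analysis, section 10.2.2 states that the "questionnaires will be summarized by descriptive statistics by visit time points".

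**The concern.** The protocol gives two QOL schedules that cannot both be followed. The calendar is the table that staff would normally use to plan visits, so its omissions could become missing data.

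Patient-reported QOL during and following treatment is a secondary objective (section 1.2.4) and a named secondary endpoint. The end-of-treatment sitting is the only assessment that the text places within the treatment period. Without it the 'during' part of the objective has no data, because the calendar goes from baseline straight to 1 month after treatment. The blanks at 12 and 24 months remove the one-year and two-year points. Since the analysis is a summary by visit, those visits would be absent from it, or only partly filled if some staff follow the text and others the calendar. A patient's own report of how they felt at a given visit cannot be reconstructed later.

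Section 2.0 also says that, to the authors' knowledge, QOL has not been evaluated with an oral supplement during chemoradiation. The protocol itself thus presents these data as filling a gap.

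**Working it through.** There is no stated power or sample-size figure to reproduce. The check sets the calendar row against the text.

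**1. Is the row read correctly?** The header has 12 columns: procedure, Screening, Pre-CRT, CRT, 1, 3, 6, 12, 16, 18, 24, ET. The QOL row also has 12 cells, so it lines up without a shift. A shift could not explain the gap in any case: the row holds seven marks including ET, and the text needs nine before ET is counted.

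**2. Text against calendar**

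| Time point | Required by | Calendar |
|---|---|---|
| Baseline | Synopsis, 5.3 | marked |
| End of chemoradiation | 5.4 | **blank** |
| 1 month | Synopsis with 5.5 | marked |
| 3 months | Synopsis with 5.5 | marked |
| 6 months | Synopsis with 5.5 | marked |
| 12 months | Synopsis with 5.5 | **blank** |
| 16 months | Synopsis with 5.5 | marked |
| 18 months | Synopsis with 5.5 | marked |
| 24 months | Synopsis with 5.5 | **blank** |

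Scheduled by the text: 1 + 1 + 7 = 9. Scheduled by the calendar: 1 + 5 = 6. Missing: 9 − 6 = 3.

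**3. Size**

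- Share of scheduled assessments: 3/9 = 33.3%. ET is left out because it is not a scheduled visit.
- Post-baseline assessments only: 3/8 = 37.5%.
- With ET counted as a tenth: 3/10 = 30%.
- With the planned 60 patients all followed to 24 months: 60 × 9 = 540 assessments by the text and 60 × 6 = 360 by the calendar. The difference is 180 for each of the two questionnaires, and it is an upper limit.

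**4. Could the blanks be intended?** Nothing in the protocol says so. QOL at 16 and 18 months but not at 12 or 24 has no stated reason. Section 5.4 orders the end-of-treatment samples and questionnaires in one sentence. The calendar marks the samples under CRT, with a footnote pointing to the last week of radiotherapy, but leaves QOL empty in that column. The column is therefore used for end-of-treatment procedures, and QOL appears to have been overlooked.

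**The case against.** The strongest reply has four parts.

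**The three blanks are not equally supported.** The end-of-chemoradiation assessment rests on section 5.4 alone. The synopsis names only the time before treatment and the follow-up visits, so the blank CRT cell agrees with the synopsis. This is fair as a description: the conflict at that point is section 5.4 against the calendar, with the synopsis silent. But silence does not cancel an explicit requirement in the body of the protocol.

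**The loss is conditional.** No passage gives the calendar precedence, and that coordinators work from it is an inference. Sites that follow the text would lose nothing. This stands, and the figures above are worded accordingly. Mixed practice would still leave the three visits incomplete for a reason the document itself created.

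**The count is a ceiling and depends on the visit list.** Deaths, withdrawals and removals would lower 180. The calendar's footnote describes visits every 3 months in the first year and every 4 months in the second, which does not match its own columns. Both points are right, but 12 and 24 months are visits under either pattern, so those two blanks do not depend on which is used.

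**The consequence is limited.** QOL is one of eleven secondary endpoints, is analysed descriptively and has no powered test. Neither primary endpoint, nor the interim analysis, nor the safety rule is touched. This stands and limits the weight of the point. It is also an inference, not a statement in the protocol, that toxicity and supplement use are greatest near the end of treatment; the conclusion does not need it.

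**Conclusion.** The point holds. The calendar omits three QOL assessments that the text requires: end of chemoradiation, 12 months and 24 months. That is 3 of 9 scheduled assessments per patient (33%; 30% to 37.5% under other ways of counting) and at most 180 patient-visits per questionnaire. The size assumes that the calendar is followed, that all 60 patients complete 24 months, and that the visit list in section 5.5 applies. The evidence is firmest for 12 and 24 months, where the synopsis and section 5.5 together conflict with the calendar; for the end of treatment it rests on section 5.4. The damage is to a secondary, descriptive objective. It should be corrected because the data cannot be recovered afterwards and the correction is small.

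**What to change.** 1. In the calendar's QOL row, add marks at 12 and 24 months, in line with the synopsis and section 5.5.
2. Add a mark under CRT with a footnote saying that it is the end-of-treatment assessment, in line with section 5.4. State one window: section 5.4 speaks of the last day, while section 5.5 and the calendar footnote place the samples in the last week.
3. Name the end-of-treatment assessment in the synopsis, so that the synopsis, section 5.4 and the calendar give the same list.
4. In the same edit, reconcile the calendar's footnote on visit frequency with its columns and section 5.5, since it describes a different follow-up pattern.

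The cost is a table correction and one added phrase in the synopsis. Compared with the current calendar, each patient has three more questionnaire sittings, all at contacts already planned; compared with the text there are none. Section 5.5 already allows the questionnaires to be given electronically or by telephone. Sample size and the primary analyses do not change. If the trial is already running, sites should be told at once, and the by-visit QOL summaries should report how many questionnaires were collected at the three affected time points.
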